**Fig. 2 Fig2:**
[figure not shown]
Proposed flow of participants through the Exercise During and After Neoadjuvant Rectal Cancer Treatment (EXERT) trial

**Fig. 3 Fig3:**
[figure not shown]
Standard Protocol Items: Recommendations for Interventional Trials (SPIRIT) Figure for the Exercise During and After Neoadjuvant Rectal Cancer Treatment (EXERT) trial

### Eligibility criteria

Men and women will be eligible for the trial if they (1) are ≥ 18 years old, (2) are scheduled to received standard NACRT consisting of 5–6 weeks of radiotherapy (45–54 Gy) with concurrent chemotherapy (orally administered capecitabine or intravenously administered 5-fluorarcil) followed by total mesorectal excision, (3) receive medical clearance to participate in the study as determined by their treating oncologist, the Physical Activity Readiness Questionnaire for Everyone (PAR-Q+), and a certified exercise physiologist, (4) are able to complete the pre-NACRT graded exercise test, (5) are not currently engaging in any regular vigorous-intensity exercise and/or ≥ 150 min of moderate-intensity-exercise/week, (6) are able to provided written informed consent and complete questionnaires in English, and (7) are willing to be randomized to exercise training or usual care (no exercise) for 12 weeks.

### Recruitment

Prospective patients will be approached by the treating radiation oncologist and study coordinator at the time of their initial radiation consultation. The study coordinator will follow-up with eligible patients by phone and schedule interested patients for pre-NACRT testing. This recruitment strategy was effective in our feasibility study with 18 of 32 patients (56%) being recruited over a 6-month period [16].

### Randomization and blinding

After completing all baseline assessments, patients will be randomly assigned to either the exercise training group or usual care group in a 1:1 ratio using block randomization. A research assistant, not otherwise involved in the trial, will generate the block sizes and randomization sequence using a computer-generated random allocation sequence which will be concealed from the recruiting study coordinator. Given the nature of the intervention, it is not possible to blind the investigators or participants to group allocation. Additionally, due to logistical challenges at our facility, it is difficult to blind outcome assessors to group allocation for the primary outcome of cardiorespiratory fitness and the secondary outcomes of functional fitness. Nevertheless, fitness outcome assessors will follow a detailed protocol and be trained in the importance of standardizing outcome assessments and avoiding bias. Moreover, outcome assessors will not review the metabolic data during the cardiorespiratory fitness test, and the criteria for achieving peak volume of oxygen consumption (VO_2_ peak) will undergo an independent review. Finally, outcome assessors will be blinded to group assignment for the exploratory outcomes of treatment toxicities, treatment completion, treatment response, and surgical complications which will be assessed by medical staff not otherwise involved in the study.

### Intervention

For patients randomized to the exercise training group, the intervention will be divided into two phases: (1) during NACRT and (2) post NACRT. During NACRT, all of the exercise sessions will be supervised by a certified exercise physiologist. We previously determined that it was feasible for patients to attend supervised exercise sessions at our fitness center (within a 5-min walk from the cancer center) since they were already coming to the cancer center 5 days/week for radiation treatment [16]. During NACRT, patients will be asked to complete 18 supervised HIIT sessions (i.e., three sessions/week for 6 weeks) and to continue with any light-to-moderate-intensity exercise that they were performing at baseline. We selected a HIIT program for evaluation because of its ability to maximize cardiorespiratory fitness improvements over a short period of time [18]. Moreover, HIIT has previously demonstrated safety and feasibility in clinical populations including patients with cardiometabolic disease [19], diabetes [20], and during adjuvant chemotherapy in patients with mixed cancers [21]. HIIT is characterized by relatively short bursts of vigorous-intensity exercise, interspersed by periods of rest or light-intensity exercise for recovery. There are an endless number of possible combinations that can make up a HIIT program; however, HIIT typically refers to exercise intensities corresponding to ≥ 85% of peak heart rate or ≥ 80% of VO_2_ peak [19]. We have designed the HIIT program in the EXERT trial to closely match a previously published HIIT program which has demonstrated feasibility, safety, and greater improvements in cardiorespiratory fitness in patients with coronary artery disease [22].

In our phase I study, we demonstrated an excellent median attendance rate of 83% to three sessions/week of moderate-intensity, continuous exercise training during NACRT [16]. Moreover, no adverse events were observed and our evaluation was that even higher-intensity exercise training would be feasible in this clinical setting. Nevertheless, the safety and feasibly of HIIT during NACRT in rectal cancer patients has yet to be established and is a key objective of our study.

In our feasibility study, the most frequently used modality was the treadmill (67.4% of sessions) [16]. Thus, the HIIT program will consist of uphill treadmill walking. Each HIIT session will start with a 5-min warm-up at a workload that elicits 30-40% of VO_2_ peak during the baseline graded exercise test. Patients will complete 2-min, high-intensity intervals at a workload that elicits 85% of VO_2_ peak during the baseline graded exercise test. Between the high-intensity intervals, the active-recovery intervals will consist of 2 min at a workload that elicits 40% of VO_2_ peak during the baseline graded exercise test. Each HIIT exercise session will end with a 5-min cool-down totaling 40 min/session. The number of HIIT intervals will begin at five and progress by one every second session up to eight intervals (Table 1).

**Table 1 Tab1:** High-intensity interval training program during neoadjuvant chemoradiotherapy in the Exercise During and After Neoadjuvant Rectal Cancer Treatment (EXERT) trial

	Interval period			Recovery period			
Session	No.	Duration	Intensity	No.	Duration	Intensity	Total duration
		(min)	% VO_2_ peak^a^		(min)	% VO_2_ peak^a^	(min)
1–2	5	2	85	4	2	40	28
3–4	6	2	85	5	2	40	32
5–6	7	2	85	6	2	40	36
7–18	8	2	85	7	2	40	40

^a^Prescribed according to workload (treadmill speed and incline) that elicited 85% of VO_2_ peak (interval period) and 40% of VO_2_ peak (recovery period) during baseline graded exercise test

Note: All HIIT sessions start with a 5-min warm-up and end with a 5-min cool-down

Prior to each exercise session, an exercise specialist will assess blood pressure and heart rate and ask patients to report any immediate symptoms. Additionally, body temperature will be assessed in patients reporting any signs or symptoms of a fever. If body temperature is ≥ 38 °C, patients will be instructed not to exercise that day. For each supervised session, the exercise specialist will record attendance and the workload (i.e., treadmill speed and incline), Rating of Perceived Exertion (RPE) (Borg 0–10), and heart rate for each high-intensity interval. Optimal adherence to the supervised exercise sessions will be facilitated by scheduled appointments, flexibility in scheduling the exercise sessions (i.e., according to patients’ radiation sessions), immediate follow-up and re-booking of missed sessions, personable exercise trainers, and free parking. In our feasibility study, we identified the most common barriers to exercising during NACRT as side effects from chemoradiotherapy (88%), fatigue (76%), and diarrhea (71%) [23]. In the EXERT trial, we will optimize adherence to the supervised exercise sessions by modifying each session according to any immediate symptoms or side effects that patients are experiencing.

If a patient is experiencing immediate side effects that hinder their ability to complete the high-intensity intervals at the prescribed workload, the fitness attendant will modify the exercise session according to what the patient is able and willing to do. Options for modifying the exercise dose will include either reducing the workload of the high-intensity intervals, reducing the number of high-intensity intervals, or both. All reasons for dose modification will be noted.

After NACRT, patients will be asked to complete at least 150 min of unsupervised, moderate-to-vigorous-intensity, continuous exercise training training/week (current Canadian Physical Activity Guidelines). In our phase I study, it was feasible for patients to achieve 150 min of mostly unsupervised, moderate-intensity exercise/week after NACRT. Although local patients in our pilot study were offered a supervised exercise program after NACRT, only two out of 16 patients expressed interest in continuing with supervised exercise in this phase and patients mainly achieved their weekly exercise minutes by walking outdoors or by using pre-existing home exercise equipment (e.g., treadmill, elliptical, and upright bike). For this reason, we felt that it would be difficult to deliver a standardized and replicable HIIT program after NACRT. Moreover, in our phase I study, cardiorespiratory fitness improved by 2.4 ml/kg/min from post NACRT to pre surgery suggesting that an unsupervised, moderate-intensity, continuous exercise training program may be effective at improving cardiorespiratory fitness after NACRT and prior to surgery in rectal cancer patients. Finally, after our experience in the phase I study, we felt that it would be feasible and safe for rectal cancer patients to complete moderate-to-vigorous-intensity continuous exercise in this phase and may result in greater improvements in cardiorespiratory fitness. Nevertheless, one of the goals of the EXERT trial is to further establish the feasibility and safety of continuous exercise training after NACRT and to determine its preliminary efficacy at improving outcomes for rectal cancer patients.

After NACRT, the exercise will be individualized according to patients’ post-NACRT graded exercise test (i.e., heart rate that corresponded with approximately 46–91% of VO_2_ peak) [24]. Patients will be provided with a heart rate monitor and will also be instructed on how to use RPE and the talk-test to determine the intensity of their exercise sessions. Patients will be provided with examples of how to complete the exercise (e.g., 30 min, 5 days/week; 50 min, 3 days/week). Moreover, patients will be instructed that the exercise completed in this phase should be in addition to what they were already doing at baseline. Finally, patients will receive printout materials with instructions on how to complete the exercise in the post-NACRT phase as well an exercise log to help them keep track of their exercise. After NACRT, optimal adherence will be achieved using a more formal behavioral support program based on the Theory of Planned Behavior (TPB) [25]. The study coordinator will maintain weekly contact with each patient via telephone and offer behavioral support sessions consisting of standard behavioral change techniques including goal setting, planning, self-monitoring, and overcoming barriers.

#### Usual care group

Patients randomized to the usual care group will receive standard medical care which includes meeting with a dietician weekly to ensure adequate caloric and nutrient intake. Patients in the usual care group will be asked not to increase their physical activity/exercise levels during or after NACRT. Exercise is not currently part of standard care for these patients at our center and patients do not receive any exercise recommendations. After the pre-surgery assessment, patients in the usual care group will be offered a copy of the Canadian Physical Activity Guidelines and encouraged to initiate an exercise program after they recover from surgery and receive medical clearance from their physician.

### Outcome measures

#### Primary outcome measure

We selected *cardiorespiratory fitness* as the primary endpoint for the EXERT trial because there is clinical equipoise as to whether 6 weeks of HIIT during NACRT is sufficient to meaningfully improve cardiorespiratory fitness. Moreover, cardiorespiratory fitness is an established surrogate for some patient-reported outcomes and clinical outcomes [9, 26–29]. Our primary measure of cardiorespiratory fitness, VO_2_ peak, will be assessed by the modified Bruce graded exercise test on a treadmill with direct measures of cardiorespiratory variables using a metabolic measurement system (Parvo Medics TrueOne® 2400; Sandy, UT, USA ) [30, 31]. The modified Bruce treadmill protocol was designed for use in high-risk and elderly individuals. Briefly, the protocol will start at 1.7 mph and 0% grade and will progress every 3 min until the patient reaches volitional fatigue or if any exercise contraindications occur. During the test, heart rate will be monitored continuously and recorded every minute and blood pressure, oxygen saturation, and rating of perceived exertion will be measured and recorded in the last minute of every stage. Immediately after the test, patients will complete a 5-min active recovery (1.7 mph and 0% grade). During the active recovery, heart rate, blood pressure, and oxygen saturation will continue to be monitored and recorded at 1 min and 5 min.

#### Secondary outcome measures

*Functional fitness* will be assessed by the Senior’s Fitness Test which measures basic mobility-related parameters associated with functional abilities in the everyday living of older adults [32, 33]. The Senior’s Fitness Test consists of six items including the 30-s chair stand (assessment of lower body strength), the arm curl (assessment of upper body strength), the chair sit-and-reach (assessment of lower body flexibility), the back scratch (assessment of upper body flexibility), the 8-foot up-and-go (assessment of agility and dynamic balance), and the 6-min walk (assessment of aerobic endurance).

*Quality of life* will be assessed by the widely used and validated European Organisation of Research and Treatment of Cancer (EORTC) core 30-item questionnaire (QLQ-C30) version 3.0 [34]. We selected the EORTC QLQ-C30 because it assesses symptoms, physical function, psychosocial function, and overall QoL [35]. The EORTC QLQ-C30 is composed of five multi-item functional scales (physical, cognitive, role, emotional, and social), three multi-item symptom scales (fatigue, nausea and vomiting, and pain), five single-item symptom scales (dyspnea, insomnia, loss of appetite, constipation, and diarrhea), a single-item financial impact scale, and a two-item global health and QoL scale. Additionally, the EORTC-QLQ-CR29 (colorectal cancer) will be used to assess QoL. The EORTC QLQ-CR29 has demonstrated acceptable validity and reliability for its supplemental use with the QLQ-C30 to assess the QoL of colorectal cancer patients during treatment [36]. The EORTC QLQ-CR29 contains 29 questions and evaluates urinary dysfunction, gastrointestinal symptoms, body image, separate concerns for persons with or without a stoma, and sexual function (separate scale for men and women). Items for both questionnaires are evaluated using a 1-week time frame (i.e., “during the past week”) on a 4-point scale (“not at all,” “a little,” “quite a bit,” or “very much”), except for the global health scale of the QLQ-30, which is measured on a 7-point scale ranging from “very poor” to “excellent.” For both the QLQ-C30 and QLQ-CR29, a higher score on the functional scales indicates better functioning, whereas a higher score on the symptom scales indicates worse symptoms.

*Overall symptom burden* will be assessed by the M.D. Anderson Symptom Inventory (MDASI) [37]. We selected the MDASI because it is brief and easy to use, and captures the most frequently reported disease- and treatment-related symptoms. The MDASI scale consists of 13 core symptom items (pain, fatigue, nausea, disturbed sleep, distress (emotional), shortness of breath, lack of appetite, drowsiness, dry mouth, sadness, vomiting, difficulty remembering, and numbness or tingling) and six interference items (general activity, mood, walking ability, normal work, relations with other people, and enjoyment of life). In addition to the 13 core symptoms, we will incorporate four additional symptoms that are specifically relevant in this clinical setting: mouth sores, hand-foot syndrome, diarrhea, and skin reaction at the site of irradiation.

*Exercise motivation* will be assessed using the TPB [25]. The key TPB constructs including attitudes, subjective norms, intention, and perceived behavioral control will be assessed using standardized items [38]. At the pre-NACRT time point, all patients will be asked to prospectively evaluate their motivation for the HIIT program. After NACRT, patients randomized to the exercise group will be asked to retrospectively evaluate their motivation for the HIIT program during NACRT and their prospective motivation for the exercise program post NACRT. Before surgery, patients in the exercise group will be asked to evaluate their retrospective motivation for the exercise program post NACRT, and all patients will be asked to evaluate their prospective motivation for exercising after surgery. All questions will be evaluated on a 5-point scale ranging from 1 (“not at all”) to 5 (“very much”).

#### Feasibility and safety

The feasibility and safety of the exercise intervention will be determined based on eligibility rate, recruitment rate, exercise adherence rate, assessment rate, and adverse events. The willingness of rectal cancer patients to be randomized to a supervised HIIT program during NACRT is unknown; however, based on the results of our feasibility study, we anticipate a recruitment rate ≥ 50% [16]. Moreover, we do not know the willingness of patients in the usual care group to return for all follow-up assessments; however, based on the results of our feasibility study, we anticipate a follow-up assessment rate ≥ 80% at each time point [16].

Exercise adherence during NACRT will be assessed by the number of exercise sessions attended out of 18 as well as adherence to the workload and duration of the high-intensity intervals. Based on the results from our phase I study [16], we anticipate a median attendance rate to the supervised exercise training during NACRT ≥ 80%. Exercise adherence to the unsupervised exercise training after NACRT will be assessed by self-report using the Godin Leisure-Time Exercise Questionnaire (GLTEQ) [39]. Based on our previous results [16] we anticipate that the mean number of moderate-to-vigorous-intensity exercise minutes post NACRT will be ≥ 222 per week. Safety will be assessed by monitoring any serious adverse events that occur during exercise testing or the supervised exercise sessions. No serious exercise-related adverse events were observed in our previous study [16].

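### HIIT attendance is scored out of a fixed 18 sessions although eligible NACRT lasts 5–6 weeks, so the arm's median attendance can be understated in proportion to the share of shorter courses

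*Protocol article*

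**What the plan says.** The Intervention section sets the supervised program during NACRT as "18 supervised HIIT sessions (i.e., three sessions/week for 6 weeks"), and Table 1 lists sessions 1 to 18. The Eligibility criteria allow "5–6 weeks of radiotherapy (45–54 Gy) with concurrent chemotherapy", and the Background describes long-course NACRT with the same range.

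The Feasibility and safety section then fixes the attendance measure: "Exercise adherence during NACRT will be assessed by the number of exercise sessions attended out of 18". Adherence to interval workload and duration is assessed as well. On the result, the section says "we anticipate a median attendance rate to the supervised exercise training during NACRT" of at least 80%, citing the phase I study, whose median attendance is given elsewhere as 83%. Feasibility and safety as a whole are to be "determined based on eligibility rate, recruitment rate, exercise adherence rate, assessment rate, and adverse events".

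**The concern.** The denominator assumes a 6-week course, but the eligible population includes patients whose course lasts 5 weeks. For them, three of the 18 sessions fall after NACRT has ended. The article describes no route to those sessions. Missed sessions are re-booked, but a session that was never available was not missed. Nothing provides for more than three sessions a week (18 in 5 weeks would be 3.6 a week) or for supervised HIIT once NACRT is over. The post-NACRT test follows within 0–7 days, and exercise then becomes unsupervised.

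The measure therefore mixes two things: how well patients attended, and how long their radiotherapy was. Establishing the feasibility of supervised HIIT during NACRT is a stated secondary objective, adherence is one of the named bases for judging it, and the trial is meant to inform phase III. Any distortion runs one way, towards making HIIT look less feasible than it was.

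**Working it through.** **Inputs.** Three sessions a week, 6 weeks and 18 sessions (Intervention, Table 1); 5–6 weeks of NACRT (Eligibility criteria); anticipated median of at least 80% (Feasibility and safety); phase I median of 83% (Intervention, Discussion); 30 patients in the exercise arm (Sample size). The share of 5-week courses is not given and is varied from 0% to 100%.

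**The plan's own figure.** Sessions = sessions per week × weeks = 3 × 6 = 18. This reproduces.

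**Ceiling by course length.** Maximum score = 3 × weeks / 18.
- 6 weeks: 18/18 = 100%.
- 5.5 weeks: 16.5/18 = 91.7%.
- 5 weeks: 15/18 = 83.3%.

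One missed session in a 5-week course gives 14/18 = 77.8%. Since 0.80 × 18 = 14.4, a score of 80% takes 15 sessions: all of them in a 5-week course, or 15 of 18 in a 6-week course. Over its own 15 sessions, a 5-week course reaches 80% at 0.80 × 15 = 12. These figures show how the scale is compressed; they do not test patients against a threshold.

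**Same attendance, different score.** Assume 83% attendance of available sessions in both groups. A 6-week patient scores 83%. A 5-week patient attends 0.83 × 15 = 12.45 sessions and scores 12.45/18 = 69.2%.

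**Effect on the arm median.** Expected median for 30 patients, from 20,000 simulated arms per share. Model A is binomial with attendance probability 0.83 per available session. Model B is beta-binomial with mean 0.80, which allows patients to differ in attendance. Both models are assumptions.

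| 5-week share | A, out of 18 | A, out of available | B, out of 18 | B, out of available |
|---|---|---|---|---|
| 0% | 83.5% | 83.5% | 85.4% | 85.4% |
| 10% | 82.5% | 83.5% | 83.2% | 85.3% |
| 20% | 81.1% | 83.6% | 81.3% | 85.4% |
| 30% | 79.4% | 83.6% | 79.6% | 85.4% |
| 50% | 76.1% | 83.7% | 76.7% | 85.4% |
| 100% | 69.9% | 83.9% | 71.2% | 85.5% |

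With the fixed 18, the expected median passes below 80% between shares of 20% and 30% in both models. With available sessions as denominator it hardly moves. The chance that the observed median reaches 80% with the fixed 18 is 95% (A) or 89% (B) at a 0% share, 68% in both at 20%, and 39% (A) or 52% (B) at 30%.

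**The case against.** The best defence is that 18 sessions are what every exercise patient is prescribed, so attendance out of 18 measures delivery of the intended dose. If that dose does not fit into a 5-week course, this is itself feasibility information. The Primary outcome measure section also speaks of 6 weeks of HIIT, which suggests that the authors planned around 6-week courses. If nearly all courses last 6 weeks, the effect is negligible. The raw data would also allow either rate to be computed later, and a condensed article may leave the handling of short courses to the full protocol.

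Much of this stands. A rate out of 18 is a valid description of dose and should stay. It answers a different question from attendance, however, and the article presents it as the adherence measure to be read against the 80% expectation. The denominator is also stated outright, so the point concerns a rule that is fixed and not a detail left out.

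Three stronger readings are tempting and not supported:
- That the feasibility result will be understated. The course mix is not given, and at a share of 0% there is no bias.
- That 5-week patients fail an 80% standard after one missed session. The 80% is an anticipated median for the arm, with no success rule attached, and adherence is one of five listed elements.
- That the phase I 83% is on a different scale. The article does not give that rate's denominator. If it was also a fixed 18, the scales match, and applying 83% to 15 available sessions would not represent the phase I experience. The 69.2% above is therefore an illustration under an assumption.

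**Conclusion.** The point holds in conditional form. The eligible course length, the 18-session program and the attendance denominator do not fit together for courses shorter than 6 weeks, and the mismatch can only lower the reported attendance.

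The size depends on an unstated course mix. Under the assumed models the expected median drops by about 1 to 4 percentage points at 5-week shares of 10–20% and still clears 80%. At 30% it drops by about 4 to 6 points and falls just short. The textual mismatch and the 83.3% ceiling are certain, given three sessions a week; the effect on the median rests on the attendance models and the assumed shares.

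The consequence is confined to the adherence part of the feasibility objective. The VO₂ peak endpoint, the sample size and the between-group comparisons are not touched.

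**What to change.** Reconcile the Eligibility criteria, Intervention, and Feasibility and safety sections on course length and number of sessions. No change to the session schedule is proposed here.

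For reporting:
- Define attendance as sessions attended divided by sessions available in the patient's planned NACRT course, that is, three per week times planned weeks, with a stated rule for part-weeks (5.5 weeks gives 16.5, so the rounding must be fixed in advance). Using the planned course keeps patients who stop early from shrinking their own denominator.
- Compare the median of this rate with the anticipated 80%.
- Report the count out of 18 beside it as delivered dose, split by planned course length.
- State which denominator lies behind the phase I 83%.

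The cost is a few sentences. Attendance is already recorded at each supervised session, and the treatment-completion outcome already uses the planned radiation completion date from electronic records, so planned course length should be obtainable. The small downside is that the per-patient rate treats 15/15 and 18/18 alike although the total dose differs, which is why both figures should be shown.

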#### Secondary objectives

The secondary objectives of the EXERT trial are to (1) compare an unsupervised, moderate-to-vigorous-intensity, continuous exercise training program after NACRT to usual care on cardiorespiratory fitness, (2) compare the supervised HIIT program during NACRT and unsupervised continuous exercise training program after NACRT on functional fitness, QoL, and symptom burden, (3) establish the feasibility and safety of the supervised HIIT program during NACRT, and (4) investigate the motivational outcomes and determinants of exercise during and after NACRT.

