#### Exploratory outcome measures

*Treatment toxicities* will be assessed by clinical nurses on a weekly basis during NACRT using the National Cancer Institute Common Toxicity Criteria for Adverse Events Version 3.0. *Treatment completion* will be assessed as the number of patients completing 100% of their planned radiation dose within 1 week of the planned completion date using electronic medical records. Additionally, the number of patients receiving ≥ 80% of their planned chemotherapy dose will be recorded. *Treatment response* will be assessed by pathologic complete response as reported by the pathologist after reviewing the surgical sample. *Surgical outcomes and complications* will be obtained from medical records.

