The results from our phase I, single-arm study demonstrated that rectal cancer patients are willing and able to participate in a supervised, moderate-intensity, continuous exercise training intervention during NACRT followed by an unsupervised, moderate-intensity, continuous exercise training intervention after NACRT [16]. More specifically, we reported an excellent recruitment rate of 56% (18/32 patients) over 6 months and a follow-up assessment rate of > 80% [16]. Moreover, the median attendance rate for the supervised exercise during NACRT was 83%. After NACRT, patients completed an average of 222 ± 155 min/week of unsupervised exercise [16]. No adverse events were observed and our evaluation was that even higher-intensity exercise would be feasible in this clinical setting [16]. Despite the exercise intervention, most health-related fitness outcomes and patient-reported outcomes declined during NACRT and recovered after NACRT [16]. Consequently, any benefit from exercise during NACRT is likely related to preventing declines in functioning. Moreover, patients reported that they experienced several benefits from exercise (e.g., physical fitness, QoL, self-esteem) but they also perceived some potential harms (e.g., worsening fatigue, diarrhea, skin irritation, hand-foot syndrome) [23]. We concluded that moderate-intensity, continuous exercise training during and after NACRT for rectal cancer is feasible and safe, and that phase II randomized controlled trials are needed to establish the benefits (and possible harms) of exercise in this clinical setting [16, 23].

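### The stated safety measure counts no event during the unsupervised post-NACRT training, although the article names the safety of that phase as a goal

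*Protocol article*

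**What the plan says.** Under Feasibility and safety, the article first gives an unrestricted basis for judging the intervention: "determined based on eligibility rate, recruitment rate, exercise adherence rate, assessment rate, and adverse events". Its last paragraph then narrows this for safety: "Safety will be assessed by monitoring any serious adverse events that occur during exercise testing or the supervised exercise sessions".

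The Intervention section divides the intervention into a phase during NACRT, with every session supervised, and a phase after it: "After NACRT, patients will be asked to complete at least 150 min of unsupervised, moderate-to-vigorous-intensity, continuous exercise" training each week. The same section states that "one of the goals of the EXERT trial is to further establish the feasibility and safety of continuous exercise training after NACRT". The closing paragraph of the Discussion says the trial is designed to give preliminary data on both benefits and harms, during and after NACRT.

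The formal objective is narrower. The third item under Secondary objectives is to "establish the feasibility and safety of the supervised HIIT program during NACRT", with no mention of safety after NACRT.

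Two other procedures bear on the point. Treatment toxicities are "assessed by clinical nurses on a weekly basis during NACRT" (Exploratory outcome measures). For exercise-arm patients after NACRT, "The study coordinator will maintain weekly contact with each patient via telephone", described as behavioral support (Intervention).

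**The concern.** A goal is stated for one phase, and the measure meant to serve it covers only the other. If the rule is followed as written, the count of training-related events after NACRT is zero whatever happens to the patients, because no training event in that phase meets the definition. Such a zero carries no information, yet it could be read as reassurance when a later trial is planned, which is the stated purpose of this one.

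The phase I study does not fill the gap. Its post-NACRT exercise was of moderate intensity, whereas EXERT asks for moderate-to-vigorous intensity. The article's grounds for expecting this to be safe are the team's experience in that study.

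A lesser gap exists during HIIT. The measure takes in only serious events, and only those inside a session or a test. A minor injury, or an exercise-related event that appears later at home, is not part of it.

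**Working it through.** There is no stated figure to reproduce. The check sets the stated data sources side by side and then sizes the uncovered period.

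**What is captured, by phase**

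| Source (section) | Arms | During NACRT | After NACRT, before surgery |
|---|---|---|---|
| Safety measure: supervised sessions (Feasibility and safety) | Exercise | Serious, in-session | None: no supervised sessions |
| Safety measure: exercise tests (Feasibility and safety; Study design) | Both | Tests before and after NACRT | Serious events at the post-NACRT and pre-surgery tests only |
| Nurse-graded toxicities (Exploratory outcome measures) | Both, blinded | Weekly | Not described |
| Symptoms before each session, reasons for dose modification (Intervention) | Exercise | Each session | None |
| MDASI, QLQ-C30, QLQ-CR29 (Study design; Secondary outcome measures) | Both | Baseline and post NACRT | Pre surgery |
| Weekly calls (Intervention) | Exercise | Not applicable | Behavioral support; no adverse-event enquiry described |
| Surgical complications (Exploratory outcome measures) | Both, blinded | Not applicable | Recorded after the phase has ended |

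The last column has no source that records events during the unsupervised training. The symptom scales come closest, but they measure severity at a visit. The two EORTC questionnaires look back one week, and none of the scales is described as relating a symptom to exercise.

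**Length of the uncovered period**

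Inputs: surgery 6–8 weeks (42–56 days) after NACRT (Abstract, Background); post-NACRT test 0–7 days after completing NACRT and pre-surgery test 7–14 days before planned surgery (Study design).

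Gap = (NACRT to surgery) − (delay to post-NACRT test) − (lead of pre-surgery test before surgery)

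- Shortest: 42 − 7 − 14 = 21 days
- Longest: 56 − 0 − 7 = 49 days

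So about 3 to 7 weeks per patient, beside 6 weeks of supervised sessions.

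**What full capture could show (context only)**

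With 30 exercise patients (Sample size) and no events, the exact 95% upper limit for the event rate is 1 − 0.025^(1/30) = 11.6% two-sided, or 1 − 0.05^(1/30) = 9.5% one-sided. These limits apply only to periods in which events are collected; under the stated rule the unsupervised training is not one of them.

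**The case against.** **The formal objective matches the measure.** Secondary objectives claims safety only for supervised HIIT, and the stated measure covers that program. This stands and lowers the severity. It does not remove the conflict, because the Intervention and Discussion sections go further than the objective.

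**The article is condensed.** Fuller adverse-event procedures may sit in the full protocol, and the Feasibility and safety section also lists adverse events without restriction. Silence alone would indeed be no finding. Here, however, the article states a rule, and that rule excludes the phase named in the goal.

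**Stronger readings the documents do not support.** A reader might infer any of the following:

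- *No comparable harm data from usual care.* Toxicities and surgical complications are compared between arms (Exploratory objectives) by blinded assessors (Randomization and blinding). Symptom scales and fitness tests are done in both arms. What lacks a usual-care counterpart is the in-session part of the safety measure.
- *The harms perceived by phase I patients go unmeasured.* The examples given in the Discussion are worsening fatigue, diarrhea, skin irritation and hand-foot syndrome. Fatigue is a core MDASI item, and diarrhea, hand-foot syndrome and skin reaction at the irradiated site are added items.
- *Nothing but in-session serious events is noticed during HIIT.* Symptoms are asked about before every session and reasons for dose modification are noted. The gap is in the stated safety measure, not in all contact with patients.
- *The unsupervised program is described as high-risk.* The Discussion applies that description to HIIT.
- *Thirty patients per arm are too few, so the safety plan is in error.* The article sets no safety threshold or zero-event criterion, so the 11.6% limit contradicts nothing in it.

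**Conclusion.** The point holds as a mismatch between goal and measure. As defined under Feasibility and safety, the measure cannot register an event during post-NACRT training, for about 21 to 49 days per patient between tests, while the article names the safety of that phase as a goal and promises harms data from it. Exercise-related events during HIIT that are not serious, or that arise outside a session, are also outside the measure, although other both-arm data give partial information on harm.

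The day range assumes that surgery and both assessments fall within their stated windows. The conclusion assumes that the safety sentence means what it says; if the full protocol collects events more widely, the article's sentence needs correcting rather than the conduct of the trial. It would go too far to predict that the phase will be reported as safe, or to say that the trial cannot assess harm at all.

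Severity is moderate. The primary endpoint, its analysis and the formal HIIT safety objective are unaffected.

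**What to change.** Extend the safety measure to all serious adverse events, and all exercise-related events of any grade, from randomisation to the pre-surgery assessment.

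- Add standard adverse-event questions to the weekly calls already made to the exercise arm after NACRT.
- Ask identical questions in both arms at the post-NACRT and pre-surgery visits, each covering the time since the previous assessment.
- Base any between-arm comparison on the visit questions only. The calls reach one arm, so including them would raise the exercise-arm count through more frequent asking.
- Report the proportion of patients with an event, with exact 95% confidence intervals.

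If this is not wanted, withdraw the post-NACRT safety goal. In either case, Secondary objectives, Intervention, Feasibility and safety, and the closing paragraph of the Discussion should be made to agree.

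The cost is a short form within existing calls and visits and a wording change. The downside is small: more events to record and attribute.
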